# Effect of inspiratory muscle training with load compared with sham training on blood pressure in individuals with hypertension: study protocol of a double-blind randomized clinical trial

**DOI:** 10.1186/s13063-016-1514-y

**Published:** 2016-08-02

**Keywords:** Blood pressure, Clinical trial, Fitness, Hypertension, Physical therapy, Respiratory exercises, Sympathetic nervous system

## Abstract

**Background:**

Hypertension is a complex chronic condition characterized by elevated arterial blood pressure. Management of hypertension includes non-pharmacologic strategies, which may include techniques that effectively reduce autonomic sympathetic activity. Respiratory exercises improve autonomic control over cardiovascular system and attenuate muscle metaboreflex. Because of these effects, respiratory exercises may be useful to lower blood pressure in subjects with hypertension.

**Methods/design:**

This randomized, double-blind clinical trial will test the efficacy of inspiratory muscle training in reducing blood pressure in adults with essential hypertension. Subjects are randomly allocated to intervention or control groups. Intervention consists of inspiratory muscle training loaded with 40 % of maximum inspiratory pressure, readjusted weekly. Control sham intervention consists of unloaded exercises. Systolic and diastolic blood pressures are co-primary endpoint measures assessed with 24 h ambulatory blood pressure monitoring. Secondary outcome measures include cardiovascular autonomic control, inspiratory muscle metaboreflex, cardiopulmonary capacity, and inspiratory muscle strength and endurance.

**Discussion:**

Previously published work suggests that inspiratory muscle training reduces blood pressure in persons with hypertension, but the effectiveness of this intervention is yet to be established. We propose an adequately sized randomized clinical trial to test this hypothesis rigorously. If an effect is found, this study will allow for the investigation of putative mechanisms to mediate this effect, including autonomic cardiovascular control and metaboreflex.

**Trial registration:**

ClinicalTrials.gov NCT02275377. Registered on 30 September 2014.

**Electronic supplementary material:**

The online version of this article (doi:10.1186/s13063-016-1514-y) contains supplementary material, which is available to authorized users.

## Background

Essential hypertension is a multifactorial disease characterized by chronically elevated systolic blood pressure (≥140 mmHg) or diastolic blood pressure (≥90 mmHg) [1–4]. Hypertension is a major risk factor for target-organ dysfunction, cardiovascular disease, and premature mortality [3, 4]. The prevalence of hypertension in Brazil has been decreasing over the past three decades, but 30 % of persons over 18 years of age still bear this condition [5].

The autonomic nervous system is a major determinant of systemic blood pressure and it might be a therapeutic target in hypertension [6, 7]. Hyperactivity of the sympathetic nervous system plays a role in abnormal elevations of blood pressure [6–8]. Blood pressure variability is increased in hypertensive persons. This phenomenon has been linked to desensitization of baroreceptors, leading to an anomalous autonomic response [9, 10]. Beta-adrenergic receptor blockers are an example of an effective pharmacologic approach to target the autonomic nervous system in hypertension [11].

Respiratory exercises are a non-pharmacologic intervention that might modulate autonomic nervous system activity and reduce blood pressure [12, 13]. An exercise composed of controlled respiratory patterns with a slow respiratory rate has improved autonomic control and reduced blood pressure in hypertensive subjects [12]. Inspiratory muscle training – a different modality of respiratory exercise – was tested in one randomized clinical trial that included 13 participants [13]; in this study, inspiratory muscle training reduced 24 h systolic blood and diastolic blood pressure by 7.9 and 5.5 mmHg, respectively, and also improved autonomic cardiovascular control. Respiratory muscle training might also have reduced sympathetic activity through attenuation of muscle metaboreflex [14, 15].

## Methods/design

### Study aim

This study aims to test the efficacy of inspiratory muscle training in reducing blood pressure in subjects with essential hypertension. It will further investigate the effects of this intervention on inspiratory metaboreflex – a putative mechanism for blood pressure reduction. The conceptual hypothesis is that inspiratory muscle training reduces mean 24 h blood pressure through modulation of sympathetic nervous system activity and muscle metaboreflex.

### Study design

This is a double-blind, parallel-group, sham-controlled randomized clinical trial. Participants are randomly assigned to receive inspiratory muscle training with a load equivalent to 40 % of maximum inspiratory pressure or inspiratory muscle training sham (no load) for 8 weeks. The study flowchart is depicted in Fig. 1. Participants are followed on weekly visits. Study outcomes are assessed at the end of the eighth week. The study timeline is summarized in Additional file 1: Figure S1, where detailed information on methods of assessment and protocols can be found.

**Fig. 1 Fig1:**
[figure not shown]
Study flow diagram. *BP* blood pressure, *ABPM* ambulatory blood pressure monitoring, *MIP* maximum inspiratory pressure; *R* randomization

### Study context

Participants will be recruited from patients receiving follow-up care at the hypertension clinic or the primary health care center at the Hospital de Clínicas de Porto Alegre, a tertiary, university-affiliated teaching hospital. Public announcements (radio, newspapers, and website) will also call for volunteers among residents of the city of Porto Alegre.

### Eligibility criteria

The study includes both male and female subjects, aged ≥35 and <65 years, previously diagnosed with essential hypertension, with a systolic blood pressure ≥140 mmHg or diastolic blood pressure ≥90 mmHg. Subjects receiving no pharmacologic therapy or taking only a thiazide diuretic are eligible to enter the study. Participants must have body mass index <30 kg/m^2^ [16], practice <150 min of moderate or intense physical activity per week, according to the International Physical Activity Questionnaire [17, 18], and have inspiratory muscle strength ≥70 % of predicted [19].

Participants are excluded from the study if they have: office blood pressure ≥160/100 mmHg; severe dyspnea; diabetes mellitus; orthopedic, musculoskeletal, or neurologic limitations; significant cognitive impairment; a current or past history of deep venous thrombosis; a history of myocardial infarction or stroke in the previous 6 months; congestive heart failure; unstable angina; or pulmonary disease of any etiology (including asthma and chronic obstructive pulmonary disease); or if they are active smokers. Women who are pregnant or breastfeeding are excluded from this study. Subjects are not eligible if they participated in another clinical trial in the previous 30 days, or if there is any other condition that might impair their ability to participate in the study or follow the protocol, at the discretion of the recruiter.

Participants are also directed not to change pharmacologic or non-pharmacologic treatment for hypertension (including changes in prescription or changes in the of level physical activity) during their participation in this study.

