### Study outcomes

The co-primary outcomes measures are changes from baseline to end of study in mean 24 h systolic and diastolic blood pressure, as evaluated by ambulatory blood pressure monitoring.

Secondary outcome measures are changes from baseline to end of study in mean daytime systolic and diastolic blood pressure; changes from baseline to end of study in mean nighttime systolic and diastolic blood pressure; heart rate variability; systolic blood pressure variability; aerobic capacity; inspiratory metaboreflex; and autonomic control.

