### Randomization, allocation, blinding, and confidentiality

A randomization sequence has been generated using Randomization.org in blocks of four to either group 1 – inspiratory muscle training with 40 % of maximal inspiratory pressure – or group 2 – sham inspiratory muscle training. An independent person not involved in this study possesses the computer-generated randomization sequence. A research assistant not involved in participant assessment obtains the code and sets the load in each device, according to randomization. A black tape hides the loading spring from the participant and from the investigators assessing outcomes.

There are no foreseen circumstances when un-blinding is permissible. When data collection is completed, the person responsible for the randomization list will provide assignment information to the investigators. Patient’s forms and other data sources are kept in a locked cabinet. Data are anonymized when entered into the database to protect confidentiality. Only investigators formally associated with the project will have access to the final study database.

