### Sample size calculation

Sample size was estimated based on a small randomized clinical trial on the effect of inspiratory muscle training on blood pressure of hypertensive subjects in Brazil [13]. That study found an 8 mmHg difference in systolic blood pressure between the active treatment and the control group (standard deviation, 10 mmHg). To detect this difference with power of 80 %, and assuming an alpha error of 5 %, the study should include 26 participants per group. We opted for a 20 % inflation of this number to account for loss of follow-up and consent withdrawal – therefore, a total of 60 participants will be included and assigned to either intervention or sham treatment.

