### Data management and statistical analysis plan

Data recorded in printed forms are kept in locked cabinets. Information is entered on Microsoft Excel spreadsheets by one person and reviewed by another. Numeric continuous variables, including blood pressure in the primary outcome measures, will be described as mean ± standard deviation or as median (interquartile range). Comparison between groups will be performed using Student’s *t* test or the Mann–Whitney U test, depending on variable distribution. As a superiority trial, differences in autonomic cardiovascular control and metaboreflex between groups will be tested with two-sided repeated-measures ANOVA. Results will be analyzed as per intention-to-treat. Participants who drop out and do not complete outcome assessment will be compared with those who completed the protocol but their data will be excluded from analysis. Statistical significance will be considered for *P* < 0.05. All analyses will be performed using PASW Statistics 18® (International Business Machines Corp., New York, NY).

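### The unadjusted test of the co-primary blood-pressure changes is valid but gives up precision: baseline 24 h pressure, and secondarily thiazide use at entry, are in hand and unused.

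*Protocol article*

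**What the plan says.** All references are to the protocol article.

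- **Eligibility criteria:** "Subjects receiving no pharmacologic therapy or taking only a thiazide diuretic are eligible to enter the study". Both groups must meet the same entry limits, including exclusion for "office blood pressure ≥160/100 mmHg". During the trial, "Participants are also directed not to change pharmacologic or non-pharmacologic treatment for hypertension".
- **Study outcomes:** the co-primary outcomes are "changes from baseline to end of study in mean 24 h systolic and diastolic blood pressure, as evaluated by ambulatory blood pressure monitoring". A baseline 24 h value is therefore needed for every participant who contributes to the analysis.
- **Randomization, allocation, blinding, and confidentiality:** "A randomization sequence has been generated using Randomization.org in blocks of four to either group 1" or the sham group. No stratification factor is named.
- **Data management and statistical analysis plan:** "Comparison between groups will be performed using" a t test or a Mann–Whitney test, chosen by the distribution of the variable. No covariate is named.
- **Sample size calculation:** for a systolic difference of 8 mmHg with SD 10 mmHg, 80% power and 5% alpha, "the study should include 26 participants per group". The total is set at 60.

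**The concern.** Two baseline quantities that may bear on the outcome are available before randomization and are left out of the comparison. Baseline 24 h pressure is half of the change score itself, and change is usually related to starting level. Thiazide use must be known for every participant because eligibility depends on it. A t test on change leaves whatever variance these explain in the error term.

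At stake is efficiency. The planned size sits barely above 80% power at 26 per arm, so a loss of precision matters more here than in a large trial. There is also a benefit in fixing the model early: allocation is released to the investigators once data collection ends, and a covariate set chosen after that point would be open to question.

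**Working it through.** **1. Inputs.** From the sample size section: difference 8 mmHg, SD 10 mmHg, alpha 5%, power 80%, 26 per group, 60 in total. I take the SD as that of the 24 h systolic change, which the article does not say outright. Not in the article, so assumed with ranges: correlation ρ between baseline and week-8 24 h systolic pressure (0.5 to 0.8); share q on a thiazide (25% to 50%); difference b between users and non-users in 8-week *change* (1 to 5 mmHg). The article gives no diastolic SD or difference, so the figures below are systolic only.

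**2. The plan's own figure.** Two-sided two-sample t test, d = 8/10 = 0.80: n = 25.52, rounded up to 26 per group. The stated figure reproduces. Power at 26 per group (noncentrality 0.80 × √(26/2) = 2.88, 50 df) is 80.7%; at 30 per group it is 86.1%.

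**3. Adjusting for baseline 24 h pressure.** With equal variance σ² at both times, Var(change) = 2σ²(1 − ρ), and the variance left after adjusting for baseline is σ²(1 − ρ²). The ratio is (1 + ρ)/2.

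| ρ | variance ratio | residual SD (mmHg) | d | power, 26 per arm |
|---|---|---|---|---|
| none (plan) | 1.00 | 10.00 | 0.800 | 80.7% |
| 0.8 | 0.90 | 9.49 | 0.843 | 84.6% |
| 0.5 | 0.75 | 8.66 | 0.924 | 90.4% |

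The gain is about 4 to 10 points. It shrinks towards zero as ρ approaches 1.

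**4. Adjusting for thiazide use alone.** Variance explained is R² = q(1 − q)b²/100, and the residual SD is 10√(1 − R²).

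| q | b (mmHg) | R² | residual SD (mmHg) | power, 26 per arm |
|---|---|---|---|---|
| 25% | 1 | 0.2% | 9.99 | 80.8% |
| 25% | 5 | 4.7% | 9.76 | 82.6% |
| 50% | 1 | 0.25% | 9.99 | 80.8% |
| 50% | 5 | 6.25% | 9.68 | 83.2% |

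The gain is 0.1 to 2.5 points.

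**5. What a chance imbalance does.** With 30 v 30 and the number of users held fixed, the between-arm difference in thiazide share has SD 11 points (q = 25%) or 13 points (q = 50%). A gap of 20 points or more has probability 7% or 20%. At 20 points the systolic comparison shifts by 0.20 × b, that is 0.2 mmHg (b = 1) to 1.0 mmHg (b = 5). The standard error of the arm difference is 10√(2/30) = 2.6 mmHg, or 10√(2/26) = 2.8 mmHg, and it already contains this source of variation.

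**6. Validity.** In a simulation with blocks of four, 30 per arm, q of 25% and 50%, b of 0, 3 and 5, and 8,000 runs each, two-sided type I error was 4.6–5.3% for the unadjusted test and 4.7–5.4% with thiazide in the model.

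**7. A limit of the formulas.** Steps 3 and 4 ignore the small price of estimating a covariate effect. In the same simulation the thiazide term moved power at 30 per arm from 86.4% to 86.0% (q = 25%) or 85.8% (q = 50%) when b = 0, and from 86.0% to 87.3% or 87.8% when b = 5. With no true gap, the term gains nothing and costs about half a point.

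**The case against.** The strongest reply is that nothing here is wrong. An unadjusted t test on randomized change scores controls its error rate. The outcome is a change, and background treatment is to be held constant, so a stable thiazide effect on the *level* of pressure cancels within each participant. The entry limits apply equally to treated and untreated people, which narrows any difference in level further. Only a difference in 8-week change could matter, and the article gives no evidence of one. Thiazide use has no special claim over age or sex as a covariate. Covariates are also commonly settled in an analysis plan, which is not shown.

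Most of this stands. A reader might infer that mixing treated and untreated participants without stratification biases the comparison. The documents do not support that: step 6 of the working shows the error rate unaffected, and the shift from a realised imbalance is part of the standard error. Nor do they support calling the blocked randomization defective; at 60 participants, stratifying on thiazide use is a trade-off.

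What does not stand is that the matter is merely left open. The article names the between-group test, and neither named test can carry a covariate. A later analysis plan could add one only by replacing what is stated here. The argument about level and change also does not touch baseline pressure, which is where most of the likely gain lies.

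**Conclusion.** The point holds as a low-severity matter of precision and pre-specification, not of bias or invalidity. The stated analysis is correct but less efficient than one using data the trial already collects.

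For the systolic outcome at 26 per arm, the baseline-pressure term is worth roughly 4 to 10 points of power. That rests on an assumed correlation of 0.8 down to 0.5, equal variances at the two times, and 10 mmHg being the SD of change. Thiazide use is a secondary covariate worth about 0 to 2.5 points, resting on an assumed gap in change of 1 to 5 mmHg and 25–50% use; it may be worth nothing. No size can be given for the diastolic outcome.

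**What to change.** In the data management and statistical analysis section, for each co-primary outcome, replace the t test or Mann–Whitney comparison with a linear model for the change in mean 24 h pressure. It should contain arm, the corresponding baseline 24 h pressure, and thiazide use at entry (yes/no). Report the adjusted mean difference with its 95% confidence interval. Fix this in writing before allocation is released to the investigators. Leave the randomization scheme unchanged.

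The cost is one or two sentences and two degrees of freedom out of about 50, with no new data. If only one covariate is kept, baseline 24 h pressure is the one to keep.

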### Study outcomes

The co-primary outcomes measures are changes from baseline to end of study in mean 24 h systolic and diastolic blood pressure, as evaluated by ambulatory blood pressure monitoring.

Secondary outcome measures are changes from baseline to end of study in mean daytime systolic and diastolic blood pressure; changes from baseline to end of study in mean nighttime systolic and diastolic blood pressure; heart rate variability; systolic blood pressure variability; aerobic capacity; inspiratory metaboreflex; and autonomic control.

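### The 5% alpha and 80% power apply to 24 h systolic pressure alone, yet systolic and diastolic pressure are co-primary, unordered and each tested at an unadjusted 0.05

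*Protocol article*

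**What the plan says.** Two outcomes share primary status. The Study outcomes section says: "The co-primary outcomes measures are changes from baseline to end of study in mean" 24 h systolic and diastolic pressure. The Abstract agrees: "Systolic and diastolic blood pressures are co-primary endpoint measures assessed with 24 h ambulatory blood pressure monitoring". Systolic is named before diastolic, but neither place calls this a testing order or says whether one or both must be significant.

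The Sample size calculation rests on one outcome. It takes from a small earlier trial an 8 mmHg "difference in systolic blood pressure between the active treatment and the control group", with an SD of 10 mmHg. It continues "To detect this difference with power of 80 %, and assuming an alpha error of 5" per cent, and arrives at 26 per group, enlarged to 60 in total for losses.

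The Background gives a diastolic effect of 5.5 mmHg from the same earlier trial. The sample size does not use it, and no diastolic SD is given.

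The Data management and statistical analysis plan section sets one threshold for everything: "Statistical significance will be considered for *P* < 0.05". The Study aim and the Discussion put forward a single hypothesis, that training lowers blood pressure, and the Discussion describes the trial as being of adequate size to test it.

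**The concern.** One hypothesis is to be judged on two outcomes of equal standing, and the article does not say how the two results combine. The usual readings lead to different properties:

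- **Either result suffices, each at 0.05.** There are two chances of a false positive, so the error rate for the blood-pressure hypothesis exceeds 5%.
- **Both results are required.** The error rate is kept, but the chance of success cannot exceed that of the weaker test, and diastolic power was never considered.

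At stake is the reading of a mixed result. If only one pressure is significant, nothing in the article settles whether the hypothesis is confirmed. That choice could then be made with the results in view.

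**Working it through.** **Inputs from the article.** Systolic difference 8 mmHg, SD 10, so d = 8/10 = 0.8. Alpha 5%, power 80%, 26 per group, 60 in total, 20% allowance for loss. Diastolic effect 5.5 mmHg (Background).

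**Assumptions.** The primary tests are two-sided (the article says so only for the ANOVA). The 5.5 mmHg is a between-group difference. The diastolic SD is 6, 7, 8 or 10 mmHg, so d = 5.5/SD = 0.92, 0.79, 0.69 or 0.55. The correlation r between the two changes is 0.5 to 0.9.

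**Step 1: the plan's own figure.** For a two-sample t test with n per group, df = 2n − 2 and the noncentrality is d√(n/2). At n = 26 this is 0.8 × √13 = 2.88 on 50 df, and power is 80.7%. At n = 25 it is 79.1%. So 26 per group reproduces for systolic pressure with a two-sided test; a one-sided test would give 21.

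**Step 2: either result suffices, each at 0.05.** Familywise error = 1 − P(|Z1| ≤ 1.96 and |Z2| ≤ 1.96), with (Z1, Z2) bivariate normal with correlation r.

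| r | Familywise error |
|---|---|
| 0 | 1 − 0.95² = 9.75% |
| 0.5 | 9.1% |
| 0.7 | 8.3% |
| 0.8 | 7.8% |
| 0.9 | 7.0% |

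**Step 3: both required, each at 0.05.** Alpha stays at or below 5%. Joint power = P(T1 > c and T2 > c), where c is the two-sided 5% critical value of t. It was obtained by simulating correlated t statistics with systolic d = 0.8. It cannot exceed the power of either test alone, so at 26 per group it is capped at 80.7%.

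| Assumed diastolic SD | Diastolic power alone, n = 26 | Joint power, n = 26 (r 0.5 to 0.9) | Joint power, n = 30 (r 0.5 to 0.9) |
|---|---|---|---|
| 6 | 90.0% | 75.8–79.8% | 82.7–85.5% |
| 7 | 79.3% | 68.6–74.9% | 76.4–81.4% |
| 8 | 68.1% | 60.5–66.6% | 68.4–73.4% |
| 10 | 49.4% | 45.3–49.3% | 52.1–55.3% |

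The last column applies if all 60 complete (60/2 = 30 per group).

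**Step 4: systolic first, then diastolic.** Systolic pressure is tested at the full 0.05, so its power is unchanged: 80.7% with 26 completers per group. With the planned 20% loss from 60, 60 × 0.8/2 = 24 per group remain and systolic power is 77.4%. Familywise error stays at or below 5%, because diastolic is tested only after a significant systolic result.

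**The case against.** A reader might infer that the stated 5% and 80% cannot both hold. The article does not support that. Its sample size section ties both figures to the systolic difference, where they are correct, and it makes no claim about joint power. Some success rules would also preserve both properties. A systolic-first order is one. Another is an either-result rule with each test at 0.025. At 26 per group its power to win on at least one outcome is about 85–91% for a diastolic SD of 6, 77–85% for 7, 73–81% for 8 and 72–76% for 10 (r from 0.9 to 0.5). Systolic power alone at 0.025 is 71.6%.

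Nor can it be said flatly that requiring both results leaves power below 80%. The shortfall depends on a diastolic SD and a correlation that the article does not give. With 30 completers per group, joint power exceeds 80% at an SD of 6 and just reaches it at an SD of 7 when the correlation is high. Many readers take co-primary to mean that both are required, and then alpha is not inflated at all. The 7–9% belongs to an unadjusted either-result rule that the article never states.

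Finally, a success rule may sit in a separate analysis plan that is not shown, and its absence from an article would not alone be a finding.

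These points limit the claim but do not remove it. The article has its own analysis section, which fixes a threshold that does not hold 5% for the single hypothesis if either unordered primary may confirm it. And the number of participants was derived from one of two primary outcomes, whatever an analysis plan says.

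**Conclusion.** The concern holds in this form: the 5% and 80% describe 24 h systolic pressure only, while the article names two unordered co-primary outcomes, applies an unadjusted 0.05 and states no success rule.

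- **Either-result rule:** the error rate would be about 7–9% instead of 5%, for an assumed correlation of 0.9 to 0.5.
- **Both-required rule:** the error rate is kept. Joint power at 26 per group would be at most 80.7%, and between about 45% and 80% over an assumed diastolic SD of 10 to 6 mmHg with the same correlations. With no dropout at all it would be about 52% to 85%.

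The systolic calculation itself is not in error. The size of any joint-power shortfall rests on the assumed diastolic SD, the correlation and the 5.5 mmHg effect.

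**What to change.** State the rule before unblinding. This is still possible: the article reports that enrolment is under way and that assignments are released only when data collection is complete.

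**Preferred wording, two sentences.** The change in mean 24 h systolic pressure is tested first, at two-sided 0.05. The change in mean 24 h diastolic pressure is tested at two-sided 0.05 as confirmatory only if the systolic result is significant, and is otherwise descriptive.

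This controls the error rate at 5% and keeps the basis on which the sample size was calculated. Enrolment need not change. The cost is that the two outcomes lose equal standing, so a diastolic-only result cannot carry the primary claim.

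**If the sponsor wants both to be required,** say so. Then state that the 80% is for systolic pressure only, and give the joint power with the diastolic SD and correlation assumed for it.
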